#### 15.3. Aggregation and Analysis Methods

The background of the study subjects is calculated and aggregated by calculating the mean value and standard deviation for continuous variables, and the frequency and proportion for categorical variables. If the continuous variable clearly does not follow a normal distribution, transform the variable appropriately, such as a logarithmic transformation, and summarize it by mean and standard deviation, or use the median and interquartile ranges as descriptive statistics.

The primary endpoint, the difference in walking distance between 30 seconds after tDCS stimulation and sham stimulation, will be assessed using a single-sample t-test or a Wilcoxon signed rank test.

For the difference in secondary endpoints, 10 m natural walking time and number of steps, Timed Up and Go test, and 360° rotation test after tDCS stimulation and sham stimulation. Evaluate with a one-sample t-test or a Wilcoxon signed rank test.

together with

Video recording of the gait state is performed to objectively analyze the change in the gait state from the perspective of a specialist (neurologist, rehabilitation doctor) when improvement is obtained.

For safety, frequency and proportion (for all subjects) for each adverse event will be evaluated.

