| Study Type                                                                    |                    | Interventional                                                                                                                                                                                                                                                                                                                                                                                                                                                                                                                                                                                                                                                                                                                                                                                                                                                                                                                                                                   |
| Study Design                                                                  |                    | Single arm study / open (masking not used) / placebo control / single assignment / treatment purpose                                                                                                                                                                                                                                                                                                                                                                                                                                                                                                                                                                                                                                                                                                                                                                                                                                                                             |

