### 7.3. Blinding

Subjects will be told whether or not they are stimulated and will not be blinded.

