| Quality of Life Assessment (PDQ-39)               |                                              | ○                |                                    |                                        |                                                       |
| Evaluation of Footfall (FOG-Q)                    |                                              | ○                |                                    |                                        |                                                       |
| Sham stimulation / SMA stimulation                |                                              |                  | ○                                  |                                        |                                                       |
| After Sham stimulation / After SMA stimulation    | Walking distance in 30 seconds               |                  | ○                                  |                                        |                                                       |
|                                                   | 10m Natural Walking Time and Number of Steps |                  | ○                                  |                                        |                                                       |
|                                                   | Timed Up and Go test                         |                  | ○                                  |                                        |                                                       |
|                                                   | 360° rotation test                           |                  | ○                                  |                                        |                                                       |
|                                                   | Video recording of walking                   |                  | ○                                  |                                        |                                                       |

|                                                  |                                              |  |   |   |   |
|--------------------------------------------------|----------------------------------------------|--|---|---|---|
|                                                  | conditions                                   |  |   |   |   |
| Sham stimulation / M1 stimulation                |                                              |  |   |   | ○ |

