| After Sham stimulation /
After M1 stimulation | Walking distance in 30 seconds               |  |   |   | ○ |
|                                                  | 10m Natural Walking Time and Number of Steps |  |   |   | ○ |
|                                                  | Timed Up and Go test                         |  |   |   | ○ |
|                                                  | 360° rotation test                           |  |   |   | ○ |
|                                                  | Video recording of walking conditions        |  |   |   | ○ |
| Adverse Events and Defects                       |                                              |  | ○ | ○ | ○ |

\*Within 3 months after the end of screening (even if you are readmitted to the hospital after being discharged from the hospital)

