### 13. Evaluation items

#### 13.1. Efficacy endpoints

##### 13.1.1. Primary endpoint (primary endpoint)

<PART1>

Comparison of 30-second walking distance between SMA and sham stimulation

<PART2>

Comparison of 30-second walking distance between M1 and sham stimulation

[Rationale for setting]

As a basis for setting the primary endpoint, patients with sloping feet may have a decrease in walking speed, but in severe cases, they may not be able to walk at all when walking, and they may not be able to achieve almost any walking distance. Even in such a case, if the walking distance is taken as the

primary endpoint, it can be left as data. On the other hand, the 10-m walking time set as a secondary endpoint may not be available for such severe cases, and the patient may have to be excluded. Therefore, walking distance was set as the primary endpoint.

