#### 13.1.3. Exploratory endpoints

Objective evaluation by videography of walking status

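### Protocol 15.3 ties the specialist video reading to a favourable result, which biases this exploratory endpoint toward benefit and does not match 13.1.3

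*Protocol*

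**What the plan says.** Section 15.3 of the protocol states the purpose of the gait video: specialists are to "objectively analyze the change in the gait state from the perspective of a specialist (neurologist, rehabilitation doctor) when improvement is obtained". It does not say which measure defines improvement, by how much, or whether it is judged patient by patient or for the trial as a whole.

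Section 13.1.3 lists the same item among the exploratory endpoints as "Objective evaluation by videography of walking status", with no condition. The schedule in 12.1 has a row "Video recording of walking conditions" under the assessments after sham and after active stimulation, in PART 1 and again in PART 2. Recording is therefore planned whatever the result.

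On masking, the Research Summary describes the design as "Single arm study / open (masking not used) / placebo control / single assignment / treatment purpose". Section 7.3 says "Subjects will be told whether or not they are stimulated and will not be blinded". It speaks of the subjects and is silent on whoever reads the video.

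The objective in section 3 is improvement of freezing of gait. The primary endpoint in 13.1.1 is, for PART 1, "Comparison of 30-second walking distance between SMA and sham stimulation", with the same comparison for M1 in PART 2. The secondary endpoints in 13.1.2 are the 10 m walk (time and steps), the Timed Up and Go and the 360° turn. The schedule row for the freezing questionnaire, which begins "Evaluation of Footfall (FOG-Q", is marked at screening only.

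**The concern.** An analysis that is triggered by a good result is not a neutral description of what happened. If recordings are read where walking improved and left unread where it did not, part of the apparent gain on video is selection. A patient whose distance rose by chance will tend to look better on video as well, as far as the two measures move together.

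This matters more here than the exploratory label suggests. The other efficacy measures after stimulation are distance, time, step counts and turning. None is defined as a count or duration of freezing, and the freezing questionnaire is not repeated. The video is therefore the only record after stimulation on which freezing itself could be seen. Subjects know their condition, and sham always precedes stimulation (5.3, 10.3). A full reading with condition concealed would thus be one of the few protections open to this design, and the wording of 15.3 gives it up.

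**Working it through.** **No stated figure to reproduce.** The protocol gives no score, test, effect size or error rate for the video analysis. The point rests first on the wording; the arithmetic only shows what the condition can do.

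**The passages side by side.**
- Recording (12.1): after sham and after stimulation, both parts, no condition.
- Endpoint (13.1.3): the video evaluation, no condition.
- Analysis (15.3): tied to improvement having been obtained.

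The third does not match the first two.

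**Inputs for the illustration.**
- Target number of patients: n = 20 (15.1).
- D = change in the measure used for selection, and V = change in the video rating (both stimulation minus sham). Both are taken as normal, in SD units, with mean 0, so there is no true effect.
- r = correlation of D and V. The protocol does not give it. Assumed values are 0.3, 0.5 and 0.7, with 0 as reference.

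**Reading A: improvement judged per patient (D > 0).**

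Mean shift: E[V | D > 0] = r × √(2/π) = 0.798 × r.
- r = 0.3: 0.24 SD
- r = 0.5: 0.40 SD
- r = 0.7: 0.56 SD
- r = 0: 0

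Share of read patients who look better: 0.5 + arcsin(r)/π.
- r = 0.3: 0.5 + 0.305/3.142 = 60%
- r = 0.5: 0.5 + 0.524/3.142 = 67%
- r = 0.7: 0.5 + 0.775/3.142 = 75%
- r = 0: 50%

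A simulation of 10,000 null trials of 20 patients gave 0.243, 0.396 and 0.561 SD, and 59.9%, 66.5% and 74.7%, in agreement.

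Suppose a one-sample t-test at two-sided 5% were applied to the selected patients (the protocol plans no such test for the video). A falsely favourable result would then occur in 10.6%, 23.0% and 46.5% of null trials. When all patients are read, the figure is about 2.5% at every r. At r = 0 with selection it is 2.3%, so nothing is added.

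**Reading B: improvement judged once for the trial (mean D > 0).**

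The mean of 20 patients has SD 1/√20, so the shift is 0.798 × r / √20 = 0.178 × r.
- r = 0.3: 0.05 SD
- r = 0.5: 0.09 SD
- r = 0.7: 0.12 SD

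The simulation gave 0.053, 0.087 and 0.130. If the trial-level condition were a statistically significant gain, the simulated shifts were larger, about 0.17, 0.28 and 0.34 SD. These are rough, because only about 2.5% of 10,000 null trials (some 250) qualify.

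**Direction.** Under every reading the shift favours stimulation when r > 0 and vanishes at r = 0.

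**The case against.** The strongest reply is that the sentence in 15.3 is loosely worded and may mean no more than a description of how gait changed in patients who improved. It contains no word such as only, it excludes nobody explicitly, and 13.1.3 is unconditional. The endpoint is exploratory in a trial that calls itself exploratory (15.1), and no score or test is attached to it. A reading procedure or the statistical analysis plan, which is not shown, could specify coded clips.

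Much of this stands. It sets the severity, and it is why two readings must be shown rather than one. It does not remove the mismatch: the condition is in the protocol's own analysis section and differs from the protocol's own endpoint list.

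A reader might infer four stronger things that the documents do not support.
- *That the video can only confirm benefit, or that selection guarantees an apparent gain.* The bias needs a correlation. Even under Reading A at r = 0.3 to 0.7, between 40% and 25% of the selected patients would not look better.
- *That harm to freezing would never be seen.* Section 2 places freezing at the start of walking and on changing direction, situations that the Timed Up and Go and the turn test include. Walking distance would register severe freezing, and adverse events are collected. What is lost is the video view of patients who did not improve.
- *That the readers know which recording follows stimulation.* No section says so. The open design and the absence of any concealment make it possible, not established.
- *That the trial's main conclusion is compromised.* The primary and secondary tests in 15.3 carry no condition on improvement.

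**Conclusion.** The point holds in limited form. Section 15.3 makes the video analysis depend on a favourable result, in conflict with 13.1.3 and with the recording schedule, and this biases the video finding toward benefit if video change and the selecting measure are positively correlated. With no true effect and correlations of 0.3 to 0.7, the shift is 0.24 to 0.56 SD if patients are selected one by one, and about 0.05 to 0.13 SD if the condition is a positive mean change in the trial. The correlations, the normal model and the existence of a numeric rating are assumptions, and the protocol does not settle which reading applies. The lack of concealment for the readers is an inference from the open design and the protocol's silence. The primary, secondary and safety analyses are unaffected. This should be fixed before any recording is read, but it does not invalidate the trial.

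**What to change.** In 15.3, delete the closing condition on improvement so that the sentence agrees with 13.1.3. State that the specialists already named read all sham and stimulation recordings of all analysed patients, whatever the walking result. Code the files and present them in shuffled order, so that readers know neither the condition nor the sequence. Sections 5.3 and 10.3 have the device removed before gait evaluation, so a recording need not reveal the condition. Report the paired sham-versus-stimulation result for all patients and label it exploratory. A defined freezing score or a formal test is optional; removing the condition does not require either.

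Concealing the order protects the reading. It does not remove any practice or fatigue effect from always giving sham first, and the report should say so.

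The cost is a wording change, file coding and some extra reading time: at most 4 sets of recordings × 20 patients = 80 sets. No new recordings, visits or staff are needed.

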#### 5.3. Clinical Research Outline

In the tDCS stimulation used in this study, it is difficult to blind the presence or absence of irritation because the patient feels discomfort in the scalp when the stimulation is actually performed. On the other hand, in order to eliminate the effects of wearing the tDCS device even in a state where no stimulation is performed (sham stimulation), evaluation is performed with sham stimulation and actual stimulation. In general, patients with Parkinson's disease have large motor fluctuations in symptoms due to drug therapy, so the patient's condition may vary depending on the timing of the examination. Therefore, when conducting a stimulation test, it is considered that an appropriate evaluation cannot be performed unless the sham stimulation and the actual stimulus are evaluated as a set.

In this study, we evaluated the efficacy and safety of SMA stimulation for sham stimulation in PART 1 and the efficacy and safety evaluation of M1 stimulation for sham stimulation in PART 2. Two tests will be conducted. In PART 1, participants will first practice various gait assessment without any intervention. Next, the tDCS device is worn on the head for 20 minutes in a resting state (sham stimulation: no actual stimulation), and then the device is removed and gait evaluation is performed. Thereafter, the tDCS device is attached again, SMA stimulation is actually performed at 2 mA for 20 minutes, and then the

device is removed and gait evaluation is performed. This is PART 1. At this point, a decision is made on whether or not to move to PART 2 in consideration of the patient's condition and the feasibility of gait evaluation for each patient. If it is judged that it is possible to migrate, the test of PART 2 will be conducted at an interval of at least 6 hours after the implementation of PART 1. In PART 2, as in PART 1, various gait evaluations are first practiced without any intervention, and then gait evaluation is performed after 20 minutes of sham stimulation with a tDCS device. After that, the tDCS device is attached again, and M1 stimulation is actually performed at 2 mA for 20 minutes, gait evaluation is performed, and PART 2 is completed.

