### [Rationale]

- 1) Transcranial direct current electrical stimulation may affect implantable medical devices and electronic devices such as deep brain stimulators, pacemakers, and defibrillators.
- 2) Transcranial direct current electrical stimulation may affect psychiatric problems such as clinically significant depression
- 3) If there is an injury or defect in the irritated part of the skull, it may cause stronger stimulation than planned.
- 4) Because it cannot be ruled out that transcranial direct current electrical stimulation can induce epileptic seizures
- 5) Since the possibility of interaction between transcranial direct current electrical stimulation and metal coils cannot be ruled out
- 6) Patients deemed unsuitable as subjects by the principal investigator are not included

## 6.3. Criteria for Transition to PART 2

When the principal investigator or co-investigator determines that there is no problem with the implementation of PART 2 after confirming the patient's general condition and the presence or absence of adverse events after PART 1

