### 10.3. Usage, dose, frequency, time required, etc.

First, practice of in front of 3 cm gait assessment without wearing the tDCS device and without doing anything. Next, the tDCS device is worn in a resting state for 20 minutes (sham stimulation), and then the device is removed and gait evaluation is performed. Thereafter, the tDCS device is attached again and cortical stimulation is actually performed at 2 mA for 20 minutes, and then the device is removed and gait evaluation is performed. These two evaluations will be one session, and the same evaluation will be performed at different stimulation sites at intervals of 6 hours or more. The stimulation site is the supplementary motor cortex (SMA) in the first (PART1) and the second (PART2) is the primary motor cortex (M1). The duration of one test is about 1 hour.

In the case of patients with Parkinson's disease with large motor fluctuations, evaluation should be performed in a state where the drug is off (that is, when the symptoms are severe after the drug wears

off, that is, Parkinson's symptoms are noticeable). However, there is no discontinuation of the medication that is actually being taken.

10.4. Guidelines for stimulation increase and decrease, etc.

The intensity and duration of stimulation should be constant, but if the stimulus is unpleasant, the stimulation intensity will be reduced.

11. Concomitant medications and concomitant therapies

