#### 13.2. Safety endpoints

Occurrence of adverse events and defects

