##### 15.2. Population to be analyzed

In principle, the target population for efficacy analysis of this study is the target population for

Intention-to-treat (ITT) analysis, which covers all cases, but the following subjects are excluded from the study population.

- 1) Those who do not meet the inclusion criteria
- 2) A person who has never taken measurements with a device.

The target population, including subjects who have undergone tDCS stimulation at least once, will be analyzed as the target population for safety analysis.

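### Section 5.3 asks about the safety of each stimulation site against sham, but the only safety summary in section 15.3 covers all subjects with no split by condition

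*Protocol*

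**What the plan says.** The outline in protocol section 5.3 describes two tests. For the first, "we evaluated the efficacy and safety of SMA stimulation for sham stimulation in PART 1"; the second is "the efficacy and safety evaluation of M1 stimulation for sham stimulation in PART 2". Safety is thus put in the same terms as efficacy, one site at a time against sham.

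Within each PART the order is sham, gait evaluation, real stimulation, gait evaluation. Section 10.3 adds: "These two evaluations will be one session, and the same evaluation will be performed at different stimulation sites at intervals of 6 hours or more". After PART 1, "a decision is made on whether or not to move to PART 2", and section 6.3 bases that decision on the patient's "general condition and the presence or absence of adverse events after PART 1".

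On analysis, section 13.2 gives the safety endpoint as "Occurrence of adverse events and defects". Section 15.2 defines one safety population: "The target population, including subjects who have undergone tDCS stimulation at least once, will be analyzed as the target population for safety analysis". Section 15.3 then gives the whole safety analysis in one sentence: "For safety, frequency and proportion (for all subjects) for each adverse event will be evaluated". The schedule in section 12.1 marks adverse events for PART 1, for the transition decision and for PART 2. Sham and real stimulation share a column within each PART.

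**The concern.** Every patient is planned to receive both sham and real current in the same session, so a proportion counted per patient over the whole study does not show which condition an event followed. Section 14.2 expects two kinds of event. Scalp symptoms arise where current is applied, whereas falls during gait evaluation can follow sham as easily as stimulation. The second kind is where a sham column is most useful, because section 5.3 includes sham to remove the effect of wearing the device.

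The denominator is a separate matter. Entry to PART 2 is conditional and depends partly on adverse events in PART 1, and section 8.1 lets undesirable events end a patient's participation. The patients exposed to M1 may therefore be fewer than all subjects and selected for having tolerated PART 1. An M1 count divided by all subjects would then look lower than the rate among those who received M1. At stake is whether the report can describe the safety of each site, which section 5.3 names as a purpose.

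**Working it through.** The plan gives no adverse event figure to reproduce. The target of 20 (section 15.1) rests on feasibility. The check is a comparison of the text and two illustrations with assumed counts.

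**Step 1. Aim against analysis.**
- Section 5.3: safety of SMA against sham, and of M1 against sham.
- Section 13.2: occurrence of events, with no comparator.
- Section 15.2: one safety set, defined by at least one stimulation.
- Section 15.3, efficacy: written as a difference between stimulation and sham.
- Section 15.3, safety: frequency and proportion of each event over all subjects, with no condition, no PART and no contrast.

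No section states a tabulation of events by condition.

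**Step 2. What one overall proportion determines.** Assume that 20 patients all receive sham and real stimulation in one PART and that 8 have a given event. The overall proportion is 8/20 = 40% in each case below.
- Event on real stimulation only: 8/20 − 0/20 = +40 percentage points.
- Event on both, in the same 8 patients: 8/20 − 8/20 = 0.
- Event on sham only: 0/20 − 8/20 = −40 percentage points.

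The same reported figure fits any difference from −40 to +40 points, so it does not determine the contrast in section 5.3.

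**Step 3. Denominator for M1.** Let m of 20 patients enter PART 2 and assume that 4 of them have an event on M1. The all-subject figure is 4/20 = 20%, and the rate among the exposed is 4/m. The ratio of the two is m/20, so the understatement is 1 − m/20 of the exposed rate.

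| m entering PART 2 | 4/m | Understatement, 1 − m/20 |
|---|---|---|
| 20 | 20.0% | 0% |
| 18 | 22.2% | 10% |
| 16 | 25.0% | 20% |
| 14 | 28.6% | 30% |
| 12 | 33.3% | 40% |
| 10 | 40.0% | 50% |

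The relative understatement depends only on m. If everyone enters PART 2, it vanishes.

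**Step 4. Scale.** One patient in 20 is 1/20 = 5 percentage points. At m = 16 the gap is 25% − 20% = 5 points, the weight of one patient.

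**The case against.** The strongest reply is that the parenthesis in the safety sentence may only say who is counted and need not forbid a breakdown. Section 15.3 is terse throughout. Its primary endpoint sentence does not separate SMA from M1 either, and that split comes from sections 5.3 and 13.1.1. The safety sentence could be read within the same two-PART structure, and a separate statistical analysis plan, not shown here, could supply the tables. Section 3 names no safety contrast, and the summary matches the endpoint in 13.2.

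Much of this stands. A reader might infer that the protocol orders events to be pooled over conditions and rules out any split; the text does not go that far. What remains is that the document states one safety summary, and that summary lacks the contrast named in section 5.3. Even if the parenthesis only names the denominator, that denominator does not fit M1 when someone stops after PART 1.

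A reader might also infer that the trial's data cannot answer the safety question. That is not supported. Events are marked by PART, scalp symptoms at the stimulated site are largely attributable to current, and the case report form may record onset. The ambiguity falls mainly on falls and on sham against stimulation within a PART.

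It is also fair to say that a table by condition would not give a clean comparison. Sham always comes first and patients know what they receive (sections 5.3 and 7.3), so order and expectation remain mixed with the effect of stimulation.

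**Conclusion.** The mismatch is real but modest. The stated safety summary does not provide the site-by-site view against sham that section 5.3 sets as an aim, and an all-subject denominator understates the M1 rate by the fraction of patients who do not enter PART 2. The example of 20% against 25% rests on assumed values, four patients with an event and 16 entrants; the protocol supports neither as a forecast. Nothing in the primary analysis depends on this table, and safety in this exploratory study of 20 is descriptive. The point concerns the stated summary and makes no claim that the raw data are inadequate.

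**What to change.** In section 15.3, state that each adverse event will be summarised descriptively by condition: PART 1 sham, SMA, PART 2 sham and M1. Use the patients exposed to that condition as each denominator and keep the overall row.

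Record the onset time and the most recent condition for every event. List separately the events that start after SMA stimulation and before or during PART 2 sham. A delayed SMA effect cannot be excluded there, and booking such events to sham without comment would flatter SMA.

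Add a sentence saying that the comparison with sham is descriptive and limited by the fixed order and the lack of blinding.

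The cost is a short change to the text and one extra recorded item per event, with no added patients, visits or procedures. The drawback is small cell counts, which is why counts should stand beside the percentages.
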